### Sample size estimation

A sample size estimation was calculated based on CRF using the 20 m shuttle run test (20 m-SRT). Previous studies reported 9 laps of improvement, with effect size of *d* = 0.31 (36) and *d* = 0.69 (37), achieved through 12 or 14 weeks of resistance-based HIIT, respectively. In the current study, a conservative effect size of *d* = 0.31 was utilised for power calculation. Therefore, based on a G*Power (Version 3.1) calculation (38) and using two groups with 80% power at an α of 0.05, it is estimated to recruit 165 participants in each group. With an average enrolment of 50 students in secondary school classes in Ningbo and a conservative 20% of dropout rate (39), it is deemed that 8 classes (approximately 50 participants per class) would provide sufficient statistical power for analysis. Given the typical scale of a Chinese secondary school (10–15 classes per grade), the 8 classes will be recruited from one secondary school.

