### Recruitment and allocation

An invitation letter will be sent to nearby secondary schools at Ningbo University. When schools express their interest, contacts will be initiated to elucidate the participation requirements. Upon agreement from the schools, invitations will be extended to head teachers and PE teachers of year 7, who will then present the study to students for recruitment. To be eligible for participation, students are required to submit signed assent forms along with signed consent forms from their parents/guardians. Students with health or medical conditions that would restrict their ability to engage in vigorous PA will be excluded from the study. The screening process will involve reviewing the medical examination reports submitted by the participants’ parents or guardians. Classes will be randomly allocated to either *PRO-HIIT* group or control group, via a computer-based random number generator by an independent researcher. The randomisation and allocation will take place after baseline assessment. The randomisation will be stratified by PE teacher, wherein each teacher's classes will be randomly assigned to either the intervention or control group.

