#### Statistical analyses

Data entry will be completed by one researcher with a random sample of at least 10% of entries cross-checked by a second researcher for accuracy. Prior to analysis, thorough checks for outliers and errors will be conducted using range and boxplot methods. Additionally, assessments for normality, homogeneity of variances and sphericity will be conducted as needed to verify assumptions. The baseline data for intervention and control groups will be presented and compared at individual level using independent sample *t*-test. An intention-to-treat approach will be adopted to evaluate the effects on outcome variables to avoid bias in exploring the impact of the intervention. Linear mixed-effect models will be used, with random effects, to analyse the impact of groups (intervention and control), timepoints (pre-, post-intervention and follow-up) and group × time interactions. Statistical analyses will be adjusted for the clustering effects at class level. Per protocol sensitivity analysis will be undertaken at the class level. Considering for disruptions such as school holidays, exams, severe weather, a minimum of 30 sessions is considered achievable over the 12-week period. Other sensitivity analyses, such as complete-case analysis, will be conducted where appropriate. Moderators, including sex (male, female), baseline overweight/obese (yes, no) and baseline CRF (healthy vs. needs to improve), will be examined with linear mixed models. Where appropriate, subgroup analyses will be conducted for the significant group-by-moderator interactions. PA, sleep and maturity will be included in the model to eliminate confounding effects. All data analyses will be conducted via IBM SPSS Statistics for Windows (SPSS 28.0; IBM Corporation, Armonk, NY, USA), with an alpha level of 0.05.

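### The rule that opens subgroup analyses names a group-by-moderator term, but in the only model described the intervention effect sits in group × time

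*Protocol article*

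**What the plan says.** All of the analysis wording is in the Statistical analyses section of the protocol article.

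- **Main model.** Linear mixed-effect models are used "to analyse the impact of groups (intervention and control), timepoints (pre-, post-intervention and follow-up) and group × time interactions". The pre-intervention value is therefore a level of the outcome.
- **Moderators.** "Moderators, including sex (male, female), baseline overweight/obese (yes, no) and baseline CRF (healthy vs. needs to improve), will be examined with linear mixed models". The terms of that model are not listed.
- **Rule for subgroup analysis.** Where appropriate, "subgroup analyses will be conducted for the significant group-by-moderator interactions". Time is not mentioned here, and no three-way term is named anywhere.
- **Adjustment.** Class clustering, physical activity, sleep and maturity are named. The baseline value of the outcome is not named as a covariate.

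The Recruitment and allocation section adds: "The randomisation and allocation will take place after baseline assessment".

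**The concern.** The moderation question is whether the effect of the intervention differs by sex, weight status or baseline fitness. With T1 as an outcome level, that effect is the arm difference in change from T1, so its moderation is group × time × moderator. The named two-way term asks something else: whether the arm difference in level, pooled over visits, differs between subgroups.

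Two things follow if the rule is applied as worded. A real moderation is diluted by a visit that cannot contain any effect, and the comparison loses the precision gained from within-pupil change. Conversely, a chance difference between arms within one subgroup at T1 enters the term and could be reported as moderation. Because the test decides whether a subgroup analysis is done, a moderator missed at this step is not followed up.

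**Working it through.** **Plan's own figure.** The Sample size estimation section gives "using two groups with 80% power at an α of 0.05, it is estimated to recruit 165 participants in each group" for *d* = 0.31. The normal approximation gives 2(1.960 + 0.842)²/0.31² = 163.3, so 164. The exact two-sided *t* calculation gives 165 (power 0.802). The figure reproduces. It concerns the main effect; no figure is given for moderation.

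**Inputs from the protocol.** Eight classes of about 50 make 400 pupils; less 20% dropout, 320. Randomisation follows T1.

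**Inputs assumed, because the protocol gives none.** A 50:50 moderator (80 pupils per arm-by-subgroup cell), SD 1, equal correlation ρ between visits, two-sided 5%. The subgroup difference in effect at T2 is D, and a share f of it persists at T3. D = 0.62 corresponds to the whole planned average of 0.31 arising in one half of the pupils. Class effects largely cancel because the moderators vary within class.

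**What the two-way term estimates.** If no three-way term is fitted, the coefficient is held equal across visits. With balanced data and equal correlations it is the three-visit average. If a three-way term is fitted, an averaged (Type III) two-way test is again that average, and a reference-coded coefficient is the difference at a single visit. None of these is moderation of change. The average is (0 + D + fD)/3 = D(1 + f)/3, that is D/3, D/2 or 2D/3 for f = 0, 0.5 or 1.

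**Standard errors.** With k = √(4/80) = 0.2236:

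- Two-way: √((1 + 2ρ)/3) × k. At ρ = 0.8: 0.931 × 0.2236 = 0.208.
- T1-to-T2 three-way contrast: √(2(1 − ρ)) × k. At ρ = 0.8: 0.632 × 0.2236 = 0.141.

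**At ρ = 0.8, D = 0.62.** For the two-way term z = 0.207/0.208 = 0.99, 0.310/0.208 = 1.49 or 0.413/0.208 = 1.99. For the contrast z = 0.62/0.141 = 4.38.

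| ρ | D | Two-way power, f = 0 / 0.5 / 1 | T1-to-T2 contrast |
|---|---|---|---|
| 0.3 | 0.62 | 24% / 48% / 72% | 65% |
| 0.5 | 0.62 | 20% / 40% / 62% | 79% |
| 0.6 | 0.62 | 19% / 37% / 58% | 87% |
| 0.8 | 0.62 | 17% / 32% / 51% | 99% |
| 0.3 | 0.31 | 10% / 16% / 24% | 22% |
| 0.8 | 0.31 | 8% / 12% / 17% | 59% |

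Simulation with class and class-by-time variance (3,000 runs, ρ = 0.8, D = 0.62) gave 18%, 32% and 49% against 99%.

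**Baseline fitness as moderator of fitness.** Splitting on T1 removes between-pupil variance. With an assumed median split at ρ = 0.8, the variance of the three-visit mean falls from 0.867 to 0.867 − (2/π) × 0.867² = 0.388, so the two-way SE is 0.623 × 0.2236 = 0.139. The contrast variance is 0.4 − (2/π) × 0.2² = 0.375, giving SE 0.137. For D = 0.62, power is 32%, 60% or 84% against 99%. At full persistence the loss is about 15 points, compared with 48 for a moderator unrelated to T1.

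**Baseline-adjusted T2 model.** Its SE is √(1 − ρ²) × k: 0.134 at ρ = 0.8 (power above 99% for D = 0.62) and 0.213 at ρ = 0.3 (z = 2.91, power 83%).

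**False positives.** With no moderation, simulated rejection was 5.6% for both tests. With an assumed class-by-sex variance of 2% of the total it was 10.1% for the two-way term and 4.7% for the contrast.

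**The case against.** The moderator model is not written out. The article names the software but not the coding or the type of test, and group-by-moderator may be shorthand for moderation of the group × time effect, or may refer to a post-baseline model adjusted for baseline. A condensed article commonly leaves exact terms to an analysis plan that is not shown. This stands to the extent that the three-visit average is an inference from the wording. It does not remove the point: the article does state the deciding term, that term does not match the only model it describes, and no baseline-adjusted moderator model is mentioned.

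A reader might infer that the rule misses most real moderation. The protocol does not support that, since it gives neither the between-visit correlation nor the persistence at T3. At ρ = 0.3 with full persistence the two-way term does slightly better than the change contrast (72% against 65%). For D = 0.31 the contrast itself has only 22–34% power at ρ = 0.3–0.6, so part of what would be missed reflects sample size and not the choice of term.

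A reader might also infer an inflated false-positive rate. The 10.1% needs a class-by-sex variance found nowhere in the protocol; without it the two tests agree.

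Further limits stand. Change over the summer holiday is a stated aim, so weight on T3 is not foreign to the trial. Academic performance has no T3, so a three-visit average does not apply to it. The calculations leave out the planned adjustment for physical activity, sleep and maturity. Moderation of effect is not among the three listed aims.

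**Conclusion.** The point holds as a minor mismatch in a secondary analysis. Taken literally, the rule tests a visit-averaged arm difference that includes a pre-randomisation visit. It recovers one third to two thirds of a T2 moderation and is open to differences already present at T1. At ρ = 0.8, with 320 pupils, a 50:50 moderator and D = 0.62, power is about 17–51% against 99%. The direction and size of the loss rest on those assumptions: it is smaller for baseline fitness moderating fitness, and absent or reversed near ρ = 0.3 with full persistence. It would go too far to conclude that the trial will test moderation wrongly, because the phrase may be shorthand for the right term. The primary comparison is not affected.

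**What to change.** In the Statistical analyses section, replace the rule with wording such as: moderation will be tested by the group × time × moderator interaction, using the T1-to-T2 contrast, with T1-to-T3 as secondary; subgroup analyses of change from baseline will follow where that test is significant. Alternatively, keep the group × moderator term but state that it is fitted to the T2 value with the T1 value as covariate. Keep the class terms in either version. If the existing phrase was meant as shorthand for one of these, the same sentence settles it.

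The cost is one sentence and a few extra parameters in the moderator models. No new data are needed.

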#### Patient and public involvement

Important input and feedback were sought from school leaders, teachers and students in the secondary schools located in Ningbo to inform and refine the study design of the *PRO-HIIT* intervention.

## Discussion

This paper outlines the study protocol for *PRO-HIIT* intervention, which aims to investigate the effectiveness of a school-based HIIT intervention on CRF, PA, body composition, muscular strength, bone health, executive function, wellbeing, enjoyment, motivation, affect, self-efficacy and academic performance in school-aged adolescents. The *PRO-HIIT* intervention will be delivered five times per week at the beginning of the three PE and two PA lessons. The PA lessons serve as a complementary opportunity for students to engage in exercises of their choice on days when PE lessons are not scheduled. The majority of school-based HIIT interventions were administered 2 to 3 times per week (15). However, the understanding of the feasibility and effectiveness of HIIT performed five times per week is limited, with only two studies identified (62, 63). Moreau et al. reported that a daily 10 min HIIT session over 6 weeks improved cognitive control and working memory in children aged 7 to 13 years (62). In addition, a 10-month of 5 × 12 min/week interval running programme was found to be feasible in a primary school setting (63). While the study reported a positive effect on sprint performance, no effects were observed on CRF, BMI, muscular fitness, and bone health. Consequently, the feasibility and effectiveness of high-frequency HIIT interventions delivered among secondary school students needs to be further evaluated. The *PRO-HIIT* study aims not only examine the effects on commonly studied variables such as body composition, CRF, muscular strength and cognition, but also to explore its impact on bone health and academic performance among 13-year-old adolescents in secondary schools.

The early pubertal phase is recognised as the time when peak bone mass accrual begins. High-impact exercises, such as resistance-based HIIT, may enhance bone mass accumulation during these crucial developmental years. Yet, there is a dearth of research investigating the association between HIIT and bone health (18). Emerging evidence suggested that both acute and chronic HIIT leads to enhanced cognitive adaptations and brain health (64, 65). However, more research is needed to understand if HIIT is beneficial to general or specific domain(s) (e.g., inhibition, working memory and cognitive flexibility) of cognitive function among children and adolescents (66). Given that cognitive function is closely linked to academic performance (65, 67), a long-term HIIT intervention has the potential to enhance academic performance. Nevertheless, only one previous study has examined the effect of HIIT on academic performance (68). The researchers found that HIIT delivered twice per week for ten weeks significantly improved academic performance on mathematics and language in the intervention group as compared to the control group. It is worth noting that this study was conducted in primary schools, warranting further investigation in diverse educational settings.

Apart from the outcome measurements, the novelty of *PRO-HIIT* study lies in its attention to the implementation process, a component often overlooked in previous school-based HIIT interventions (15). The present study will scrutinise the intervention process with the guidance of the MRC process evaluation guidelines, thereby enhancing the understanding and facilitating the dissemination of the *PRO-HIIT* study. Another novelty of the *PRO-HIIT* study is its aim to determine the extent of potential fitness loss over the two-month summer holidays and how a school-based intervention may mitigate this decline, thereby contributing to the examination of the SDH. Furthermore, existing HIIT interventions in schools have predominantly taken place in western countries (15). Cao et al. (69) found that a running-based HIIT intervention conducted in a school setting improved body composition and CRF amongst Chinese secondary school students. It should be noted, however, that the study exclusively focused on obese adolescent boys, limiting its generalisability to the broader healthy population. The *PRO-HIIT* study will address this gap by providing valuable insights on the benefits of school-based HIIT within an Asian cultural context.
